## Abstract

Childhood renal tumors account for around 6% of all childhood cancers and 90% of these cases are Wilms tumor. In Europe, the SIOP-RTSG approach is considered standard of care and has resulted in five-year survival rates of over 90%. Efforts to decrease toxicity are now being pursued. Short-term fasting (STF), a short but strong reduction in calorie-intake, is associated with improved fitness, enhanced coping with acute physical stress and a lower risk of age-associated diseases. STF temporarily reduces growth to boost resilience, maintenance, and defense-mechanisms, by which toxic side-effects of (oxidative) damage and inflammation are largely prevented. Renal surgery for Wilms tumor carries a risk of acute kidney injury (AKI) and pediatric patients that had an episode of AKI are at increased risk for developing chronic renal disease. STF could mitigate surgery-induced stress and could further improve outcomes. We aim to investigate the effect of STF on renal function recovery after renal tumor surgery by conducting a single-center, prospective, randomized, non-blinded, intervention study. Children diagnosed with a unilateral renal tumor and opting for curative treatment are eligible for inclusion. The main study objective is to investigate the potential decrease in occurrence of AKI due to STF. Secondary objectives include renal function recovery, child's wellbeing, physical functioning, and feasibility of and adherence to STF in children with cancer.

## Introduction

Childhood renal tumors account for around 6% of all childhood cancers (1–3). Most of these cases represent Wilms tumor (WT), also known as nephroblastoma (1–3). About two-thirds of patients with Wilms tumor are diagnosed before the age of 5 years and 95% are diagnosed before the age of 10 years (4), the median age at diagnosis is 43 months for girls and 37 months for boys (5). In Europe, the Renal Tumor Study Group of the International Society of Pediatric Oncology (SIOP-RTSG) guidelines are conducted as best available care and survival is excellent, equal to outcomes from COG-RTG in the USA (3, 6–10). The SIOP-RTSG strategy advocates treatment at dedicated centers and includes preoperative chemotherapy, surgery, and risk-tailored postoperative radiation- and/or chemotherapy (6, 11–15). Preoperative chemotherapy decreases tumor rupture risk during surgery and therefore largely reduces the consequent need for postoperative radiotherapy (16). It downstages the tumor and identifies an extra adverse risk group; the blastemal-type WT, which is considered a high-risk tumor that needs intensified treatment (3, 15). Use of these international regimens, centralization of care, multimodal treatment, response tailored stratification, supportive care strategies and multidisciplinary management have resulted in a significant improvement in survival, with a current overall five-year survival rate approaching 90% (6, 7, 12–15). Therefore, we can also focus on reducing treatment toxicity, which affects long-term quality of life and survival. One of the most striking toxicities after renal tumor treatment is renal function impairment due to sacrificing a substantial percentage of kidney tissue by tumor-nephrectomy, the use of nephrotoxic chemotherapy and, in incidental cases, (high dosage) radiotherapy. Also, a substantial proportion of WT patients carries a germline predisposition which increases not only kidney cancer risk, but also the risk of early kidney failure (17).

An intervention to reduce and/or prevent toxicity is caloric restriction (CR) (18–22). CR, also known as dietary restriction (DR), is defined as a reduced intake of calories, mostly with compensation of vitamins and minerals and without causing malnutrition (23). CR has shown to be associated with extended life span, lower risk of age-associated diseases, improved fitness, and enhanced coping with acute physical stress (18–22). CR can be applied to delay aging or as nutritional preconditioning method before and/or during therapy (18, 22, 24–26). Alternatively, a more stringent and acute method can be used: short-term fasting (STF), which can be performed right before a period of (surgery-induced) stress (22, 27, 28). Recent studies have shown preventive effects of CR and/or STF on aging, genomic stress, ischemia-reperfusion injury (IRI) and acute stress conditions (22, 25, 26, 28–34). Nutritional preconditioning by e.g., CR/STF has been proven feasible and safe in well-nourished patients before living-kidney donation (35–37) and was effective in improving radiological and pathological response during neo-adjuvant chemotherapy treatment for breast cancer (38).

CR and STF redesign energy usage by reducing growth via inhibiting growth hormone (GH) release and decreasing circulating IGF-1, while boosting resilience, maintenance, and defense mechanisms (26, 34, 39–41). Possible explanations for the effect of reduced IGF-1 on longevity are the increased corticosterone levels as a compensatory mechanism and an increase in IGF-BP1, leading to a reduced number of active IGF-1 molecules (42). In addition to reduced GH concentration, the thyrotrophic axis is also downregulated by CR, resulting in decreased concentrations of thyroid stimulating hormone and thyroid hormones (43). During surgery, systemic (IRI-)injury and subsequent formation of reactive oxygen species is unavoidable, leading to elevated cell death and inflammation (44). The protective state induced by CR and STF may reduce the extensiveness of this generalized inflammatory response (31, 33, 34, 39, 45, 46).

Following short-term injury and toxicity experienced by children with cancer, adult survivors of childhood cancer are at risk for long-term nephrotoxicity, i.e., renal dysfunction and high blood pressure (47–51). In limited studies available, an increased risk of severe renal impairment was identified in unilateral WT-survivors (50, 52, 53). In a follow-up study of unilateral WT-survivors, 21% had stage II chronic kidney disease (CKD) (50). In another study in WT-survivors, 53% developed stage II CKD and hypertension was noted in 40% (54). Hence, adult survivors with a solitary kidney have a high relative risk of developing (end-stage) renal disease and this is most likely due to reduced renal mass/eGFR-reserve (55, 56). Pediatric patients that had an episode of acute kidney injury (AKI) are at increased risk for developing chronic renal disease, including hypertension and end-stage renal disease (49, 57, 58). Postoperative AKI is also associated with increased morbidity and longer hospital stay and the magnitude of this risk depends on the severity of AKI (59, 60). STF could potentially reduce hyperfiltration and oxidative stress, specifically on the contralateral kidney, and might therefore lower the risk and extent of acute and late nephrotoxic effects.

To investigate whether STF reduces toxicity and postoperative renal damage, we aim to conduct a single-center, prospective, parallel-group, non-blinded, randomized controlled trial in pediatric patients with renal tumors. These children follow a strictly planned treatment schedule and are in a relatively well condition in comparison with other pediatric oncology patients. This allows implementation of the study-intervention, which can provide further knowledge on the effects of preoperative fasting in pediatric patients. The primary objective of our study is to determine the effect of STF on the occurrence of AKI after tumor-nephrectomy. This study will also further enhance insight into the mechanism and the effect of STF.

## Methods and Analysis

The Fasting Intervention for children with Unilateral Renal Tumors to reduce Toxicity Study (FIURTT-Study) will be conducted at the Princess Máxima Center for Pediatric Oncology, Utrecht, which is the centralized pediatric oncology hospital for all pediatric cancer patients in the Netherlands.

### Study Population

Eligible participants are children with a clinical suspicion of a unilateral malignant renal tumor, without metastatic disease, at the Princess Máxima Center. A diagnosis of a renal tumor, based on MRI, is necessary for participating in the study. Eligible patients will undergo the SIOP-RTSG UMBRELLA regimen (15). Inclusion criteria are a unilateral localized renal tumor for which radical unilateral tumor-nephrectomy is planned and an adequate understanding of the Dutch language. Children will be excluded if they meet any of the following criteria: bilateral renal involvement, low body weight (for subjects younger than 1 year: SD-score < -2 for weight by age, for subjects older than 1 year: SD-score < -2 for weight by height), an underlying metabolic disease, metastatic disease, metachronous disease or no curative treatment possible.

### Intervention

When a child and their caregivers agree to participate, the child will be randomized into a treatment arm. The randomization follows a balanced stratification procedure, per age-group and gender. Subjects randomized to the control arm will follow the normal preoperative guidelines: this includes no intake of food/solids/milk products from 6 h before surgery, but intake of clear liquids (including glucose-rich clear liquids) is allowed until transfer to the preoperative anesthesia care unit. When a subject is randomized to the intervention arm, he/she will undergo the preoperative fasting diet. The duration of STF depends on age: i.e., based on the study from van Veen et al. (61), to avoid unnecessary risk of developing hypoglycaemia. Subjects will be admitted to the hospital 1 day before surgery and therefore STF will be pursued during admission.

The fasting period in the defined age groups are (also shown in figure 1):

- Group 1: 6–24 months (0,5 to 2 years): 10 h of fasting.- Group 2: 2–7 years: 14 h of fasting.- Group 3: 7–18 years: 18 h of fasting.

STF is defined as absence of any caloric intake; subjects are free to drink unlimited water, tea, and other clear liquids without calories to maintain a sufficient fluid balance.

### Study Procedures

Subjects will be assessed for blood glucose levels 2 h before the planned time of surgery. If a subject shows any symptoms suggestive of hypoglycaemia (somnolence, trembling, sweating, pale skin color, tachycardia, and/or irritability) during the fasting period, an additional point-of-care blood glucose test will be performed. Escape medication has been defined in the study protocol in the case of hypoglycaemia. For both treatment arms we standardized the induction of anesthesia, maintenance of anesthesia, postoperative pain relief, timing of surgery and IV-fluids for the first 24 h after surgery. General anesthesia will be induced and maintained with Sevoflurane. IV-fluid used during surgery is Kydialite (1% glucose), according to the estimated maintenance requirements following the 4/2/1 rule: 4 cc/kg/hr for the first 10 kg, 2 cc/kg/hr for the second 10 kg, and 1 cc/kg/hr for every kg above 20. It can be supplemented with Ringers lactate at the discretion of the anesthetic team. IV-Fluids during the 24 h after surgery are Ringer's lactate solution or equivalent, according to standard of care protocol (maintaining a diuresis of 1 cc/kg/hr).

Non-invasive interventions that will be conducted during study runtime are questionnaires to analyse aspects of wellbeing and the potential burden of the intervention, wearing an accelerometer and physiotherapeutic assessments. Subjective wellbeing will be analyzed using the PEDSQL-Cancer Module parent form (62, 63). Physiotherapeutic assessments will consist of a short questionnaire to gather information on physical functioning and strength [the SARC-F, (64)], measurements of (skeletal) muscle mass using leg circumference, ultrasonography of quadriceps muscles using a portable linear transducer [Philips Lumify, Philips N.V., Best, The Netherlands (65)] and body composition using bio-electrical Impedance Analysis [Bodystat, QuadScan 4000, Isle of Man, United Kingdom (66)]. Motor function will be evaluated using the Gross Motor Function Measure [GMFM-88 (67)]. Invasive procedures and study appointments will coincide with standard procedures to reduce the burden of participation. Tissue biopsies will be acquired from the removed kidney after diagnostic samples have been taken. Further details and an overview of all procedures are provided in the Appendix III: Study Workflow.

### Primary Outcome

Our primary outcome is AKI on postoperative day 3, 48–72 h after surgery. AKI is defined according to the KDIGO-guidelines (68). The percentage of subjects developing AKI will be measured in both treatment arms. Laboratory measurement of serum creatinine (μmol/L) will be assessed by routine lab procedures and urine output (mL/kg/h) will be calculated by routine clinical procedures. eGFR will be automatically calculated using both the Chronic Kidney Disease Epidemiology Collaboration (CKD-EPI) formula and the Revised Schwartz Equation for Glomerular Filtration Rate (Schwartz-formula).

### Secondary Outcomes

Our secondary endpoints comprise several aspects of the preoperative fasting diet and the postoperative recovery. All the secondary outcomes will be compared between the study arms to identify a possible influence of STF.

- The occurrence of the substages of AKI will be assessed on postoperative day 3. Substages are defined according to KDIGO guidelines (68). Laboratory measurement of creatinine (μmol/L) will be assessed by routine lab procedures and urine output (mL/kg/h) will be calculated by routine clinical procedures.- Postoperative renal function will be assessed using laboratory measurements, including creatinine (μmol/L), cystatin-C (mg/L), urea (mmol/L), albumin (g/L) and eGFR (ml/min), all assessed by routine lab procedures. These outcomes will be used to determine the postoperative recovery of renal function.– Renal tissue injury will be investigated on postoperative day 0, 1, 2, 3 and 28. It will be estimated by urine analysis for biomarkers Neutrophil Gelatinase-Associated Lipocalin [NGAL, (69)] and Kidney Injury Molecule-1 [KIM-1, (70)]. These biomarkers will be checked using routine lab procedures at set time points.- Change in fasting parameters will be calculated using blood samples taken on the day before surgery and on the day of surgery. Laboratory values investigated by routine lab procedures are fasting glucose (mmol/L), fasting insulin (pmolU/L), albumin (g/L), IGF-1 (nmol/L), growth hormone (hGH, mU/L), fT4 (pmol/L), reverse-T3 (nmol/L), fT3 (nmol/L), TSH (mE/L) and β-Hydroxybutyrate (mmol/L).- Subject wellbeing will be determined via the PedSQL Cancer Module questionnaire (62, 63) and the internally developed behavior questionnaire. Another internally developed questionnaire will be used to investigate the burden of intervention. These questionnaires will be taken at set time points before surgery, at the end of admission and 1 week after surgery.- Physical activity will be measured via an accelerometer [ActiGraph wgt3x-bt (71)]. Participants will wear the accelerometer in the 7 days before surgery and for another 7 days from postoperative day 4. Open-source software will be used to evaluate physical activity levels during the pre- and postoperative period.- Physiotherapy assessment will be performed twice. This assessment will evaluate (skeletal) muscle mass [leg circumference, quadriceps muscle ultrasonography (65)], body composition (bio-electrical impedance analysis) and gross motor function (GMFM-88) (67). In children who can walk independently for over 6 months, information on physical functioning and strength will be assessed via SARC-F questionnaire (64).- Postoperative hospital admission time will be measured in days since surgery.- Occurrence of peri-operative complications will be carefully assessed. Important complications, such as perioperative tumor spill, hematoma, (wound) infection, intussusception and hypoglycaemia will be investigated and reported in percentages.- Body weight will be assessed regularly during study runtime at set time points. It will be compared between both study groups and between time points (f.i. pre- and post-fasting).- Blood pressure will be assessed regularly during study runtime at set study visits and during hospital admittance. We will collect data on blood pressure (mmHg), presence of hypertension (yes/no) and use of anti-hypertensives (yes/no).- Blood samples and the tissue biopsies obtained will be used to determine upregulation of cytoprotective genes and anti-inflammatory markers associated with the fasting state. Appendix II provides extensive information regarding the histological and molecular analysis. In general, the samples will be used to conduct an expression analysis of genes responsive to fasting, e.g., cytoprotective antioxidant genes, GH/IGF1, and DNA damage and toxicity markers.

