### Statistical Analysis

Statistics will be computed using IBM SPSS software version 25.0 (Chicago, IL, USA) or R version 4.0.3 or newer. An intention-to-treat analysis will be conducted to account for the feasibility of the diet. A two-sided significance level of 0.05 will be used for all primary and secondary analyses unless stated otherwise. An analysis will be performed with multiple imputation in the case of missing data. All preoperative / baseline characteristics will be described for the intervention group and the control group. To determine the primary endpoint, we will calculate the proportion of AKI present on postoperative day three after radical nephrectomy in the two treatment arms. Results will be compared by using a Chi-square test for 2 proportions.

In the secondary analysis, a multivariable logistic regression model will be estimated to study the treatment effect of fasting on the occurrence of AKI, adjusted for confounders such as age, sex, weight and compliance to the diet. Additionally, a multinominal logistic regression model will be estimated to investigate the treatment effect of fasting on the substages of AKI. Proportions of substages of AKI will be compared by using the Chi-square test for equality of proportions generalized to more than two independent samples. Due to the presence of repeated measurements, mixed models will be estimated for the following outcomes: postoperative renal function, postoperative renal tissue injury, change in physical activity, quality of life and body weight, to investigate the effect of STF. Confounders such as age, sex, and an interaction term between time and group will be incorporated in each mixed model. Adherence to the diet and occurrence of side effects will be reported as percentage. Change in metabolic, endocrine, and fasting parameters, clinical parameters of mobilization, duration of in-patient hospitalization, occurrence and duration of ICU admission, physiotherapy assessment, occurrence of perioperative complications and upregulation of cytoprotective genes and inflammatory markers will be compared between the two treatment groups by using the *t*-test in the case of continuous outcome variables or non-parametric test in case of violations of normality assumption. The Chi-square test will be used for categorical data.

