## Discussion

With this single-center, prospective, parallel-group, non-blinded randomized controlled trial, we aim to determine the effect of short-term fasting on acute kidney injury, treatment toxicity and postoperative recovery in pediatric patients diagnosed with a Wilms tumor. Our study will provide information on the merits of caloric restriction, in the form of short-term fasting, and its possible future application and possible implementation in pediatric oncology care.

Nutritional preconditioning represents a non-invasive and cost-effective method that could mitigate the effects of acute surgery-induced stress and (postoperative) toxicity. It has previously been associated with health benefits when exerted prolonged against age-related diseases and more acute as preconditioning method against treatment related toxicities, including kidney transplantation surgery and neoadjuvant chemotherapy in adults. It has however, never been applied to children during cancer treatment, who need to cope with treatment-related toxicities during treatment and for decades after successful curation from cancer. A potential drawback observed in some initial adult clinical trials are issues with adherence to the dietary regimen. We have tried to circumvent this issue by including expertise and advise of parents from the Society Childhood Cancer Netherlands (Vereniging Kinderkanker Nederland) into the design of our study. We expect to increase feasibility of our study by, amongst others, scheduling of surgical operations in the morning, thereby having most of the fasting period during the night, making fasting easier, especially for young children. Additionally, smell of and temptations to food are minimized by adjusting room location in the hospital and special door signs indicating a child is fasting. To investigate whether preoperative short-term fasting contributes to a clinically significant reduction in acute kidney injury after radical nephrectomy for a unilateral renal tumor in pediatric patients, without being a significant burden on the pediatric patient, this randomized clinical trial is indicated. It could significantly reduce the extent of treatment-related toxicity, therefore reducing disease burden in the short- and long-term.

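### The preoperative accelerometer week includes the admission day, so the reference for change in physical activity is partly recorded during the fast, in the fasting arm only

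*Protocol article*

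**What the plan says.** All places are in the protocol article.

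- **Secondary Outcomes:** "Participants will wear the accelerometer in the 7 days before surgery and for another 7 days from postoperative day 4". Activity levels are then evaluated for the pre- and postoperative periods.
- **Intervention:** "Subjects will be admitted to the hospital 1 day before surgery and therefore STF will be pursued during admission". The fasts are "Group 1: 6–24 months (0,5 to 2 years): 10 h of fasting", "Group 2: 2–7 years: 14 h of fasting" and "Group 3: 7–18 years: 18 h of fasting". For controls, "this includes no intake of food/solids/milk products from 6 h before surgery", and glucose-rich clear liquids remain allowed after that.
- **Statistical Analysis:** mixed models are planned for several outcomes, among them "change in physical activity, quality of life and body weight", each with a time-by-group interaction.
- **Discussion:** surgery is scheduled in the morning so that most of the fast falls at night. Measures to limit food cues include "adjusting room location in the hospital and special door signs indicating a child is fasting".

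Nothing shown removes the admission day or the fasting hours from the preoperative activity period.

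**The concern.** A reference period for a change outcome should end before the arms are treated differently. Here it runs up to surgery, while the fast runs from the admission day to surgery. The fast therefore lies inside the reference period.

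The overlap differs between arms. For surgery between 08:00 and 12:00, controls stop solids between 02:00 and 06:00 on the day of surgery, so none of their waking hours on the admission day are affected. An 18 h fast starts between 14:00 and 18:00 on the admission day, and a 14 h fast between 18:00 and 22:00.

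Elsewhere the article treats this same interval as time under the intervention: fasting parameters are compared between the day before and the day of surgery, and body weight is compared before and after fasting. Only for activity does the interval count as preoperative reference.

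If fasting children move less in those hours, the fasting arm's preoperative level falls. Its decline to the postoperative week then looks smaller, and the time-by-group term shifts in favour of fasting without any postoperative benefit.

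**Working it through.** The article gives no sample size, effect or power figure for the accelerometer outcome, so there is no stated figure to reproduce. The check sizes the overlap.

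**Inputs from the article:** a 7-day window before surgery; admission one day before; fasts of 10, 14 and 18 h; controls without solids from 6 h before; surgery in the morning; 50 patients randomised 1:1.

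**Assumptions not in the article:** surgery at 08:00 (varied to 12:00); awake 07:00 to 20:00, with activity spread evenly over those hours; activity reduced by a fraction d = 0.5 while fasting; shares of the three age groups as shown below.

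**Share of clock time:** 10/168 = 6.0%, 14/168 = 8.3% and 18/168 = 10.7%. Most of this is sleep, so waking hours matter more.

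**Waking hours of the fast on the admission day (h), surgery at 08:00:**
- 10 h fast: starts 22:00, h = 0.
- 14 h fast: starts 18:00, h = 2.
- 18 h fast: starts 14:00, h = 6.

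The hour from 07:00 to 08:00 on the day of surgery is set aside, because both arms are then without solids.

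**Bias.** Waking wear time is 7 × 13 = 91 h. If the two arms have the same usual activity and the same postoperative activity, the difference in change between arms is d × h/91 of baseline.

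| Fast | h/91 | Bias at d = 0.5 |
|---|---|---|
| 10 h | 0% | 0% |
| 14 h | 2/91 = 2.2% | 1.1% |
| 18 h | 6/91 = 6.6% | 3.3% |

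**Average over the arm** (assumed shares of the 10/14/18 h groups):
- 28/50/22%: (0.50 × 2 + 0.22 × 6)/91 = 2.32/91 = 2.5% of hours; bias 1.3%.
- 20/60/20%: (0.60 × 2 + 0.20 × 6)/91 = 2.40/91 = 2.6%; bias 1.3%.
- 22/50/28%: (0.50 × 2 + 0.28 × 6)/91 = 2.68/91 = 2.9%; bias 1.5%.

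**Sensitivity:**
- Surgery at 10:00: the 14 h fast starts at 20:00, so h = 0; for the 18 h fast h = 4, 4/91 = 4.4%, bias 2.2%.
- Surgery at 12:00: 14 h group 0%; for the 18 h fast h = 2, 2/91 = 2.2%, bias 1.1%.
- Bedtime 22:00 in the oldest group, surgery at 08:00: 8/105 = 7.6%, bias 3.8%. The arm averages become 1.4 to 1.6%.
- No activity at all while fasting (d = 1): the biases double.

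**Effect on a test.** With 25 per arm and an assumed SD of change of 25% of baseline, the standard error is 25 × √(2/25) = 7.07. A bias of 1.3% gives a noncentrality of 1.3/7.07 = 0.18. The two-sided 5% t-test with 48 df then rejects in 5.4% of trials when there is no postoperative effect. At a bias of 1.5% the figure is 5.5%.

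**Cost of six days.** With ICC the within-child correlation between days, the variance ratio of the baseline mean is (ICC + (1 − ICC)/6)/(ICC + (1 − ICC)/7) = 1.042, 1.021 and 1.010 for ICC 0.3, 0.5 and 0.7.

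**The case against.** The strongest reply is that the sentence sets a wear schedule and not an analysis rule. The article does not say that all seven days are averaged, and it does not define time in the mixed model. If time were the calendar day, the admission day would be its own time point. Wearing the device during the fast is also legitimate, since the secondary outcomes are meant to cover the fasting diet as well as recovery.

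This stands in part: the data collection is not at fault, and the choice of days can be settled at analysis if the records are dated. It does not remove the point. The article gives one preoperative window, evaluates activity over the pre- and postoperative periods and analyses change. Following that as written puts the fasting hours into the reference.

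The objections on size stand. Day-before admission is not limited to one arm, so the general effect of being in hospital should cancel. The 10 h group has no extra waking overlap. The 18 h group is probably a minority, since the Introduction puts 95% of Wilms tumor diagnoses before age 10 and about two-thirds before age 5.

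A reader might infer from the room arrangements that fasting children are less active for the whole admission day, which would give a larger bias. The Discussion does not support this. It describes moving rooms and marking doors to limit the smell and temptation of food, and says nothing about confinement or restricted movement.

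**Conclusion.** The point holds as a minor flaw of definition. On the plain reading, part of the reference period for change in physical activity is recorded under the intervention in the fasting arm only.

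The size is small: about 1 to 1.5% of baseline over the arm, arising mainly in the 18 h group, and less with later surgery. This rests on assumed surgery at 08:00, assumed waking hours and age shares, and activity halved during the fast. The direction is conditional too: it favours fasting only if fasting lowers activity, on which the article has no data.

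A reader might go further and infer that the trial is set up to make fasting look protective. The documents do not support that. The shift in the false-positive rate is about half a percentage point under the assumptions shown. It concerns one of many secondary outcomes, and the primary AKI outcome is unaffected.

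**What to change.** Add one sentence to the outcome definition: in both arms, the preoperative activity level is computed from the full days before the admission day (days -7 to -2), and the admission day is reported separately by arm as activity during the fast.

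The wear schedule and clinical care stay as they are. Where data have already been collected, the same rule can be applied by leaving the admission day out of the baseline in both arms. The price is six baseline days in place of seven, or about 1 to 4% more variance in a child's baseline mean for day-to-day correlations of 0.7 down to 0.3. In return, the overlap with the fast falls to zero in every age group, and any acute effect of fasting on activity is still reported.
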